**4.8 Maintenance of trial treatment randomization codes and procedures for breaking codes.**

Randomized allocation to one of two treatment arms after assessment of eligibility, and after obtaining informed consent from the patients for participation.

The patients selected for participation will be randomly assigned to either the control (enhanced medical care) or intervention group (manualized psychotherapy based on PIT principles) by a computer generated multi-block randomization schedule using the program “Rand”. This randomization schedule will be generated at the Coordination Centre for Clinical trials. The schedule will be a 1:1 ratio, permuted in setting blocks of 4, 6 and 8 patients. Randomization

will also be stratified by participating hospitals and settings. The concealment of treatment allocation is ascertained through central allocation in the KKS Düsseldorf by fax. The trial is not blinded to patients or staff treating them as this is impossible with the intended trial design.

**4.9 Identification of any data to be recorded directly on the CRFs (i.e. no prior written or electronic record of data), and to be considered to be source data.**

The primary outcome and the majority of secondary outcomes are self report questionnaires that are considered to be part of the case report forms.

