## 9. Statistics

### 9.1. Description of the statistical methods to be employed

The data will be listed per center, per setting and per patient. Descriptive statistics will be calculated for each treatment group. Demographic and baseline data will be compared using appropriate statistical techniques.

For confirmatory analysis a modeling approach will be applied. The null hypothesis tested is: no treatment difference between control and intervention group with respect to the primary endpoint. A linear model with mixed effect will be used:

$$y_{i,j,c,s(c)} = \mu + \alpha_j + \eta_c + \zeta_{c,s(c)} + \varepsilon_{i,j,c,s(c)},$$

where  $y_{i,j,c,s(c)}$  is the response of individual  $i$  ( $i=1, \dots, m_{c,s}$ ) randomized to treatment  $j$  ( $j=1, 2$ ) for center  $c$  ( $c=1, \dots, C$ ) and setting  $s(c)$  ( $s(c)=1, \dots, n_c$ ). The notation indicates two treatment assign, and two level of stratification (patients within settings and settings within centers) with number of settings varying within centers. The total number of observations per treatment group is  $\sum_c \sum_s m_{c,s}$ .

The fixed-effects parameters in the model are  $\mu$  (the grand mean) and  $\alpha$  (the group effects). The random effect  $\eta$  indicates center effect,  $\zeta$  setting effect and  $\varepsilon$  measurement error. These three random variables will be assume statistically independent each other, with mean zero and component of variances  $\tau_\eta$ ,  $\tau_\zeta$ , and  $\tau_\varepsilon$  respectively.

The parameters of interest in this analysis are the mean of the control group  $\mu + \alpha_1$  and the contrast of means  $\alpha_1 - \alpha_2$  (which indicates treatment effect).

Estimation of model parameters will be calculated with REML (restricted maximum likelihood) method. Treatment effect will be tested with a likelihood ratio test (LRT at the alpha-level of 0.05). Additionally, centers and settings effect will be predicted with the best linear unbiased predictors (BLUPs) of the random effects. Asymptotic confidence intervals will be reported for all parameters in the model.

Distributional assumptions will be assessed (e.g. residual analysis) and transformation on the response variable will be done if it is necessary. Additionally, if adjustments for covariates are necessary they will be included in the model.

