### 9.3.A demonstration of the potential for recruiting the required number of suitable subjects within the intended period

A pilot study was performed in all trial centres in November and/ or December 2004. All consecutive patients in the collaborating somatic departments were pre-screened and patients without evident reasons for exclusion (major organic disease, age ) were asked for their informed consent to take part in the pilot assessment and interview. Variations in rates of pre-screening exclusions are mostly due to different percentages of organically explained disorders in the different settings. Patients were given the SOMS-7 (see 5.9) and those above cut-off took part in an excerpt of the SCID-Interview to test for presence of Multisomatoform Disorder (MSD) and were checked for other inclusion and exclusion criteria as defined in 5.6. Eligible patients were informed about the planned study orally and with written material, afterwards they were asked whether they would agree to take part in this study if it became available.

| Trial Centre              | Weeks of screening | Number of assessed out of total patients seen (N) | Eligible patients w. MSD (N) | Patients agreeing to take part (N) |
|---------------------------|--------------------|---------------------------------------------------|------------------------------|------------------------------------|
| Heidelberg    | 3                  | 90 out of 120                                     | 17                           | 14 (19 per month)                  |
| Düsseldorf  | 3                  | 38 out of 52                                      | 8                            | 6 ( 9 per month)                   |
| Hannover      | 2                  | 10 out of 25                                      | 6                            | 6 ( 12 per month)                  |
| München       | 2                  | 20 out of 32                                      | 6                            | 4 ( 8 per month)                   |
| Münster     | 3                  | 11 out of 168                                     | 6                            | 6 ( 8 per month)                   |
| Regensburg  | 4                  | 26 out of 200                                     | 6                            | 6 ( 6 per month)                   |

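### Asymptotic intervals for all model parameters do not suit about 6 centres and 9 settings: the control-mean interval is somewhat too narrow if sites differ, and Wald intervals for the centre and setting variances are unreliable (minor; treatment contrast unaffected)

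*Protocol*

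**What the plan says.** Protocol section 9.1 specifies a linear mixed model for the primary endpoint. Treatment group is fixed; centre, setting within centre and error are random, each with its own variance component. On estimation it says: "Estimation of model parameters will be calculated with REML (restricted maximum likelihood) method". On the targets of inference it says: "The parameters of interest in this analysis are the mean of the control group", to which it adds the treatment contrast. The treatment effect is tested by a likelihood ratio test at 0.05. On intervals it says: "Asymptotic confidence intervals will be reported for all parameters in the model". It mentions no degrees-of-freedom or other small-sample correction.

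Section 9.1 puts no numbers on the centres or settings and says only "with number of settings varying within centers". The best guide is section 9.3: "A pilot study was performed in all trial centres in November and/ or December 2004". Its table has six rows. The setting footnotes give 1, 2, 1, 1, 2 and 2 settings per centre, nine cells in all.

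Section 4.8 states that randomisation is 1:1 and "will also be stratified by participating hospitals and settings".

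**The concern.** The control mean carries the centre and setting effects with it. Its precision therefore depends on how many centres and settings there are, and adding patients within the same sites does not remove that component. With 6 centres there are at most 5 degrees of freedom between centres. With 9 cells in 6 centres there are 9 − 6 = 3 for settings within centres, because three of the six centres have a single setting and cannot separate the two effects. A normal quantile treats the estimated between-site variances as if they were known.

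At stake are the intervals around the control-arm level and around the between-centre and between-setting variances. The method is stated in the protocol, so this is not a case of detail left to an SAP. If 9.1 is followed literally, the control-mean interval may claim more precision than the design can give, and the variance intervals may be uninformative or include impossible values.

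**Working it through.** **Inputs from the protocol.** SD 12.5 and difference 6.25 (section 9.2); 88 per group, so 2 × 88 = 176 patients (section 9.2); 1:1 allocation within hospital and setting (section 4.8); REML with random centre and setting (section 9.1). The 6 centres and 9 cells are counted from the section 9.3 table.

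**Assumed.** Centre and setting ICCs from 0 to 0.10, and patients spread equally by centre or equally by setting. The protocol gives neither.

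**Check of the plan's own figure.** It states no coverage or ICC, so only the scale can be checked: n = 2 × 12.5² / 6.25² × (0.84 + 1.96)² = 62.7, rounded up to 63 per group, as printed in section 9.2.

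**Bounds for the control mean.** A ±1.96 interval whose standard error rests on exactly 5 df covers 89.3%, roughly the floor. The t quantile on 5 df is 2.571, and 2.571 / 1.960 = 1.31, so that interval is 31% wider.

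**Simulated coverage of the nominal 95% interval, estimate ± 1.96 SE** (section 9.1 model, REML, 1,500 runs per case; each range spans the two patient spreads):

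| ICC centre / setting | Control mean | Treatment contrast |
|---|---|---|
| 0 / 0 | 95.3–95.5% | 94.1% |
| 0.01 / 0.01 | 94.1–94.2% | 94.2% |
| 0.025 / 0.025 | 93.3–93.4% | 94.3% |
| 0.05 / 0.05 | 92.3–92.6% | 94.3% |
| 0.10 / 0.05 | 90.3–90.8% | 94.3% |
| 0.10 / 0.10 | 90.7–91.1% | 94.3% |

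The Monte Carlo SE near 95% is √(0.95 × 0.05 / 1500) = 0.6 points. The contrast stays close to nominal because it is estimated within cells, on about 176 − 9 − 1 = 166 residual df.

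A second simulation (1,200 runs per case, 176 patients) gave 95.8% for the control mean at 0/0, 95.0% at 0.01/0.01, 93.7% at 0.025/0.025, and about 92% at both 0.05/0.05 and 0.10/0.05. Satterthwaite intervals in the same runs covered 94 to 96.5% throughout. A fixed t on 5 df covered 96.6 to 97.5% when both ICCs were 0.05 to 0.10 and 98.1 to 99.3% at smaller ICCs. It over-corrects there, so an estimated-df method is preferable.

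**Size in PCS points, at ICCs 0.05/0.05.** Total variance is 12.5² = 156.25, so centre and setting variances are each 7.81 and the residual is 140.63. Approximately, SE² = 7.81/6 + 7.81/9 + 140.63/88 = 1.30 + 0.87 + 1.60 = 3.77, and SE = 1.94. The half-width is 1.96 × 1.94 = 3.8 with z and 2.571 × 1.94 = 5.0 with t on 5 df, a difference of about 1.2 points.

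**Variance components, idealised.** If a variance estimate were a scaled chi-square on d df, the Wald interval would be the estimate times 1 ± 1.96√(2/d). Its lower limit is negative whenever d < 2 × 1.96² = 7.7.

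| d | Wald multiples | Exact multiples | Wald coverage | Log-scale coverage |
|---|---|---|---|---|
| 5 | −0.24 to 2.24 | 0.39 to 6.0 | 81.6% | 91.5% |
| 3 | −0.60 to 2.60 | 0.32 to 13.9 | 76.4% | 89.3% |

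**Variance components, simulated from the actual model.** Wald coverage was 92.5 to 100% for the centre variance, 73.5 to 100% for the setting variance and 93.3 to 93.8% for the residual variance. The estimate fell on the zero boundary in 19 to 70% of runs for centre and 20 to 76% for setting. Coverage near 100% in such cases is not reassurance: the true variance is small or zero, and the interval is wide and reaches below zero.

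**The case against.** The strongest reply is that nothing the trial decides on is affected. The hypothesis concerns the treatment difference, randomisation is stratified by hospital and setting, and the interval for the contrast holds close to its nominal level in every case. That stands, and it is why the point is minor.

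Four further objections stand in part.

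- **Control mean.** A reader might infer that its interval is simply wrong. The protocol does not support that. With no site differences, coverage is nominal, and the shortfall depends on ICCs the protocol does not give. Even at 0.05/0.05 the extra half-width is at most about 1.2 PCS points, below the 2.5 that section 9.2 lists as a small change.
- **Meaning of asymptotic.** A reader might infer that impossible, below-zero variance limits are planned. They follow only from a symmetric Wald interval, which 9.1 does not name. Log-scale and profile-likelihood intervals also rest on large-sample theory and respect the zero boundary. The wording permits the Wald form; it does not require it.
- **Which variances.** The chi-square multiples are an illustration. REML components are not scaled chi-squares, and the simulated centre variance did not under-cover consistently. The residual variance is estimated well.
- **Number of sites.** Six centres is well supported, since the pilot ran in all of them. Nine settings, and hence 3 df, is read from pilot footnotes; the trial's settings could differ.

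The objection that the interval type belongs to the SAP carries less weight. An SAP often fixes it, but here the protocol already commits to a type for every parameter.

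**Conclusion.** The concern holds as a minor point. The stated interval method suits the contrast and the residual variance. It does not suit the control mean if sites differ, nor the centre and setting variances. For the control mean, a nominal 95% normal-theory interval covers about 95% at ICCs of 0 to 0.01, 93 to 94% at 0.025/0.025, and 90 to 93% at a centre ICC of 0.05 to 0.10. For the two between-site variances, symmetric Wald intervals are unreliable and can fall below zero.

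This rests on three assumptions: the ICC range, 6 centres with about 9 cells, and reading asymptotic as normal-theory intervals. A reader might go further and infer that the treatment comparison or the trial's conclusion is compromised. The simulations show no such effect.

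**What to change.** In section 9.1, replace the commitment to asymptotic intervals for every parameter with two statements. Fixed effects (control mean and treatment contrast) get t-based intervals with Satterthwaite or Kenward-Roger degrees of freedom. Centre and setting variance components get profile-likelihood intervals. Stating the planned numbers of centres and settings in the same section would remove the need to infer them.

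The cost is small: a software option, no new data, and a treatment comparison left essentially unchanged. The control-mean interval becomes somewhat wider. Satterthwaite was simulated and held close to nominal; Kenward-Roger was not simulated. Profile-likelihood intervals avoid negative limits but are still large-sample intervals on very few units, so those for the centre and setting variances should be read as rough.

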## 4. Trial design

### 4.1. Primary and secondary endpoint

#### Primary endpoint

The primary purpose of this study is to assess if patients who fulfil diagnostic criteria from multisomatoform disorder with predominant pain symptoms and who receive manualized psychotherapy based on PIT principles (test group) will or will not show improved quality of life in comparison to controls who receive enhanced medical care (control group). The primary analysis will be based on the German version of the SF-36 Health survey short form (Bullinger and Kirchberger 1998). The statistical hypothesis will be based on the Physical Component Score of SF- 36. (t 0, t 1, t 2)

Statistical hypothesis:

H0: *no treatment difference between control and test group*

vs.

H1: *difference between control and test group*

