**Interpretation of differences between study arms concerning type of intervention and time spent with the patient**

The design of the trial incorporates a confounding of type of intervention and time spent with the patient. Hence, this design does not control for unspecific effects of time spent with the patient. As a result, we will not be able to confirm the specificity of psychodynamic-interpersonal therapy for the treatment of patients with MSD.

This is acceptable because a) the main aim of the trial is a pragmatic one: is there anything effective that can help such patients as there is such limited evidence for effectiveness? If there is sufficient evidence that this treatment is beneficial, specificity can be addressed in later studies. b) To confirm specificity would involve a more elaborate and costly design, ideally a three limbed study PIT vs counselling vs. enhanced medical care. For one type of functional somatic syndrome, PIT has already been shown to be specific (Hamilton et al. 2000).

**4.5 Expected duration of subject participation and description of the sequences and duration of all trial periods, including follow-up**

The expected duration of subject participation is 16 months overall: A 4-week-period for screening, randomization and pre-therapy investigation, a 12-week-period for 12 weekly sessions of manualized psychodynamic-interpersonal psychotherapy or control intervention, final assessment after three months and follow-up-investigation 12 months after completion of therapy.

(For more details of trial schedule see trial diagram, Supplement 2)

**4.6 Description of the „stopping rules“ or „discontinuation criteria“ for individual subjects, part of trial and entire trial**

There are no predefined statistical stopping rules and no interim analyses in this trial.

Premature study termination can be due to the following reasons:

- Trial Steering or Data Monitoring and Safety Committee recommend to stop the trial
- Risk-benefit ratio is changed in relevant degree (e.g. through new external information)

A study site can be closed prematurely for the following reasons:

- Major protocol violations
- Inadequate patient recruitment
- Non-Compliance to the study requirements

For criteria for individual subject withdrawal see 5.3

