**7.2. Methods and timing for assessing, recording, and analysing of efficacy parameters**

Efficacy parameters will be assessed before and after the treatment period and after one year. Most efficacy parameters are self-report data. In addition, there will be an assessment of psychophysiological measurements at three month.

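### The confirmatory model omits the baseline PCS that the trial collects, and leaves covariates and transformation open without a criterion or decision time

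*Protocol*

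**What the plan says.** Section 9.1 sets the confirmatory analysis: "A linear model with mixed effect will be used". The equation contains a grand mean, a treatment effect, a random centre effect, a random setting effect within centre, and error. The sentence that starts "The fixed-effects parameters in the model are" lists the grand mean and the group effects and nothing else, so there is no baseline PCS term.

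Two open rules close the section. After residual checks, "transformation on the response variable will be done if it is necessary". Then: "Additionally, if adjustments for covariates are necessary they will be included in the model". Neither rule names a covariate, a transformation, a criterion or a time of decision. Separately, near its start, the section says "Demographic and baseline data will be compared using appropriate statistical techniques".

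A baseline PCS is available. Section 4.1 schedules PCS at t 0, t 1 and t 2, and section 7.2 states "Efficacy parameters will be assessed before and after the treatment period and after one year". Section 4.3 includes the SF-36 in the eligibility assessment, and section 4.8 places randomisation after eligibility and consent. Section 4.5 describes the opening of the trial as "A 4-week-period for screening, randomization and pre-therapy investigation".

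Supplement 5, by contrast, names sex and age in advance as covariates for the heart rate and heart rate variability analysis.

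**The concern.** There are two separate matters.

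- **Precision.** An outcome measured before and after treatment usually correlates with itself. A model without the baseline value leaves that share of the variance in the error term, and the confidence interval is wider than the data require. Section 9.2 itself worries about power: it notes how strongly the sample size depends on the effect size and raises the number from 63 to 88 per group.
- **Openness of the primary test.** The protocol writes the model and then lets both its covariates and its outcome scale change on an undefined condition. Section 9.6 requires deviations from the statistical plan to be justified, but a covariate or transformation added under these clauses would arguably not count as a deviation. More than one primary p-value is therefore compatible with the plan. A transformed PCS would also leave the points scale on which section 9.2 defines the 6.25-point target and the 2.5, 4.5 and 6.5-point thresholds for important change.

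**Working it through.** **Inputs from the protocol.** SD 12.5, difference 6.25 points, two-sided alpha 0.05, two-group normal test, and 63 and then 88 per group (section 9.2); 1:1 allocation (section 4.8).

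**Assumption.** The correlation r between baseline and one-year PCS is not in the documents. The values 0.3, 0.5 and 0.7 are assumed.

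**Step 1: reproduce the plan's figure.** n = 2 × 12.5² / 6.25² × (0.84 + 1.96)² = 8 × 7.84 = 62.7, so 63 per group, as stated. Power at 63 is 80.1%. The baseline is not used anywhere in this calculation.

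**Step 2: effect of adjusting for baseline.** The residual SD becomes 12.5 × √(1 − r²), the standard error of the difference is that SD × √(2/88), and power is Φ(6.25/SE − 1.96).

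| r | Variance removed (r²) | SE at 88 per group | Power at 6.25 points | n per group for 80% power |
|---|---|---|---|---|
| none | 0% | 1.88 | 91.3% | 63 |
| 0.3 | 9% | 1.80 | 93.5% | 58 |
| 0.5 | 25% | 1.63 | 96.9% | 48 |
| 0.7 | 49% | 1.35 | 99.6% | 33 |

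Worked example for r = 0.5: SE = 12.5 × 0.866 × 0.1508 = 1.63; 6.25/1.632 − 1.96 = 1.87; Φ(1.87) = 96.9%.

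The table assumes that all 88 per group give a one-year PCS, because section 9.2 states no dropout rate. The 91.3% is the formula at the fixed planning values. It is not the 79.6% median that section 9.2 reports from its own simulation, in which the effect and SD vary.

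**Step 3: the same at a smaller effect.** With 88 per group, power is 80% at an effect size of 2.80 × √(2/88) = 0.422, or about 5.3 points. Adjustment raises that 80.0% to 83.5%, 89.9% or 97.5%.

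**Step 4: what the open clauses permit.** Simulation with no treatment effect, 88 per group, 8,000 runs for each r, normally distributed scores, no centre or setting effects, nominal level 5%:

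| Rule | r = 0.3 | r = 0.5 | r = 0.7 |
|---|---|---|---|
| Fixed unadjusted | 5.2% | 5.0% | 4.7% |
| Fixed adjusted | 5.0% | 4.7% | 5.0% |
| Adjust only if a baseline test is significant | 4.9% | 4.4% | 3.5% |
| Better of unadjusted and adjusted | 6.6% | 7.1% | 8.1% |
| Best of four (adding a log transformation) | 8.2% | 9.1% | 10.5% |

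Either analysis holds its level when fixed in advance. Inflation appears only when the analysis is selected by its result.

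**The case against.** The strongest reply has four parts.

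- **The unadjusted comparison is valid.** Randomisation makes it unbiased, and its standard error already allows for chance baseline imbalance. This stands: leaving out baseline PCS forgoes efficiency and is not an error of inference. At 88 per group and 6.25 points the gain is about 2 to 8 percentage points of power.
- **Covariate lists and transformation criteria commonly belong in an SAP.** That is true of detail the protocol leaves unsaid. Here the protocol writes the confirmatory model itself and attaches the open clauses to it, so it fixes the matter badly and does not simply defer it.
- **The data-driven mechanism is partly inferred.** A reader might conclude that covariates enter after the baseline comparisons, or that both choices are made with arm labels visible. Section 9.1 says neither. The sentence on baseline comparisons is not linked to the covariate clause, residual analysis is linked only to the distributional assumptions and transformation, and residuals can be examined without treatment labels. The text supports only that it does not say when or how the choices are made. The most obvious trigger, a significant baseline test, did not inflate the error rate.
- **The timing of t 0 is uncertain.** The order of words in section 4.5 suggests that the pre-therapy investigation follows randomisation, but it lists the contents of a four-week period and does not define a sequence. The trial diagram is not available in the text reviewed. Nothing shows whether the screening SF-36 is the t 0 form.

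**Conclusion.** The point holds as one of precision and prespecification. The printed confirmatory model leaves out a baseline measure that the trial collects, and two clauses leave its covariates and outcome scale undetermined.

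The size depends on a correlation that the documents do not give. Over 0.3 to 0.7, the standard error at 88 per group falls from 1.88 to between 1.80 and 1.35 points. Section 5.1 requires an SF-36 score at least one SD below the norm. This narrows the baseline range if it applies to PCS (the section does not say which score), so the lower half of the range is safer to rely on.

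A reader might go further and infer that the primary result is biased or that its type I error is inflated. The documents support neither. The 6.6–10.5% range is what the wording permits if the most favourable analysis is chosen, not what it must produce. The change is worth making because it is nearly free and removes the ambiguity; the trial's primary test is not invalid without it.

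**What to change.** In section 9.1, before any outcome data are seen by arm:

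- State the primary model as one-year PCS = treatment + baseline PCS (fixed, linear) + centre + setting within centre, with centre and setting random as now.
- Define baseline PCS as a value recorded before randomisation, since patients are not blinded. Confirm whether the screening SF-36 is the t 0 form.
- Remove the conditional covariate and transformation clauses from the confirmatory analysis and analyse PCS on its own scale.
- Make any other adjustment or transformation a named sensitivity analysis.

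The sample size can stay at 88 per group, with the gain taken as precision. The cost is wording in section 9.1, because PCS is already scheduled at t 0. If the screening and t 0 forms turn out to be separate and t 0 follows randomisation, the screening PCS must also be kept as trial data, which the protocol does not state.
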